### **3.3 Recontact and consent**

Research assistants (RAs) will contact this cohort by telephone to screen for eligibility and invite them to participate in the proposed study (see script and screening questions in Appendix A). Interested, eligible patients will be invited to provide consent over the telephone (see consent form in Appendix B). The RA will read the consent form to the patient, answering questions and providing clarification as needed. The RA will document consent on the form and will sign the form. A copy of this signed consent form will be mailed to participants or sent electronically following the consent process. The telephone call will be audio-recorded for quality control and to ensure that a, audio record of the verbal consent process is saved. If participants prefer to view the consent form prior to screening, a copy will be sent by mail or electronically and a follow-up call will be made to re-assess interest.

We are seeking to obtain verbal consent because written consent may not be feasible in the current context, with postal service delays. Participants may not be able to easily return signed consent forms through the mail. As mentioned above, the project must be completed within a 6-month timeframe, with funders recognizing that there is an urgent need among the target population and a need to assist family physicians to handle anxiety and depression symptoms during and after pandemic waves. Having to wait for consent forms to be returned before proceeding may lead to significant delays. The study and intervention are very low risk, with the self-care tools having already been tested in full RCTs and with participants, having already completed the study described in section 3.2, already being familiar with standard study procedures. Participants will have a mailed copy for their records to refer back to as needed.

### **3.4 Data collection from patient participants**

Following consent, RAs will conduct the baseline interview (see Appendix C) with participants. Measures to be collected are as follows:

- Symptoms of depression: We will use the PHQ-9, a widely used 9-item measure of depression severity to determine presence and type of depressive symptoms. The PHQ-9 was selected based on its wide use in medical populations, established severity ranges and sensitivity to change, validation as a screening measure, and inclusion of somatic symptoms which are recognized as a core domain of depression, not confounding diagnosis in patients with chronic disease. The criterion for clinically-significant depression is 10 (but as specified above, this is not being used as an eligibility cut-point).
- Severity of anxiety symptoms: The seven item GAD-7 will be used as a continuous measure of severity of anxiety symptoms (internal consistency: Cronbach  $\alpha = .92$ ; test-retest reliability: intraclass correlation=0.83). Scores range from 0-21. The criterion for clinically-significant anxiety is 10 (also not used as an eligibility cut-point)
- Alcohol abuse: The 4 item CAGE questionnaire with a score ranging from 0-4 will be used to detect alcohol abuse and dependence. Although a cut point of 2 or more is used conventionally (average sensitivity 0.71, specificity 0.90), the cut point of 1 or more results in greater sensitivity as expected, and has been used in some studies. We will categorize as: no, possible (score of 1), or probable (score of 2+).

- Other baseline data: include questions on hospitalizations and ED visits during the previous 6 months, COVID diagnoses in patient or family, current living arrangement, having a family caregiver, and current homecare services.

At 8 weeks, with an anticipated follow-up rate of 75% (120 end of project interviews), the PHQ-9, and GAD-7 will be re-administered, along with enquiry into use of the self-care materials, perceived helpfulness in managing mental health problems, satisfaction with the intervention, and use of health services including any counseling or therapy started, during the 8-week study period. Satisfaction will be measured with a 3-item version of the Client Satisfaction Questionnaire (CSQ-3), highly correlated with the CSQ-8 ( $r=0.94$ ).

Additionally, RAs, coaches and the coach supervisor will carefully track information required to address the feasibility objective using dedicated follow-up logs and checklists.

### **3.5 Interventions**

The interventions to be evaluated in the RCT are: 1) the algorithm-determined self-care tools, matched to the specific mental health symptoms reported by participants, and 2) the tools plus up to 3 coach calls. All participants receive the self-care tools; only one group receives the coaching. This design allows us to evaluate the feasibility and acceptability of the tools, and the additional benefit (if any) of the coaching. Coaching is expected to increase use of the tools.

The tools and the coaching manual will be adapted from those we have successfully deployed in the DIRECTsc depression self-care project focusing on patients with depressive symptoms, but abbreviated to meet the needs of the proposed short-term intervention for a broader sample of patients to include those with anxiety symptoms and with minimal symptoms. Tools will include individual chapters of the Antidepressant Skills Workbook, the mood monitoring tool, a workbook on managing worry; relaxation audio files and information on exercise and healthy eating (see Toolkit contents described in Appendix D). In view of the short duration of the intervention (8 weeks), a maximum of 2 tools will be sent to each participant.

An algorithm will determine which self-care tools, matched to the specific mental health symptoms reported by participants, will be couriered to the participants. The study coordinator will apply the algorithm (using a paper form) to the participant's baseline results. An administrative assistant will be available at the Research Centre to assemble the required tools and arrange for them to be couriered to participants' homes using a secure courier service we have used in previous studies. Along with the tools, participants will be sent a welcome letter describing their study group assignment, and what to expect next (coach calls, if relevant, and expected timeline for the follow-up questionnaire).

Coaching by a trained lay coach will be structured and guided by a manual. Trained lay coaches will call participants in the week following delivery of the toolkit to guide them through the self-care toolkit over an 8-week period. Coaches will contact participants a maximum of 3 times, with calls expected to average 15-20 minutes. Call content will be guided by a structured coaching manual adapted from those used in our previous two RCTs. The coaches will follow structured agendas, keep records of all contacts, and will be trained to follow-up on any reported suicidal thoughts and to identify if there is intent to act, using a previously-developed protocol (which includes referring these participants to the coach supervisor for proper follow-up, see section 3.7 below).

The coaches will be bilingual (English, French), with excellent organizational and interpersonal skills, but without formal training in CBT (e.g., psychology undergraduate students). In previous

research, we have successfully used both psychology undergraduate students and others. The personal characteristics and maturity of the individual will be the most important criteria used to select coaches. They will be trained during a half-a day training session led via Zoom, based on the Coach Manual (see Appendix E - Coach manual) and mock practice sessions conducted over the telephone. Coaches will be trained and supervised by the coach supervisor, [name] (psychotherapist and PhD candidate, McGill Clinical Psychology, fully bilingual). AB is familiar with the DIRECT-sc intervention, has worked with co-investigators previously, and has been involved with planning the adaptation of the intervention to suit the current study. Her previous experience with intervention development and student supervision are matched to the requirements for the coach supervisor, and her experience working as a Psychosocial Intake Counselor and Crisis Management Services Coordinator will allow her to follow-up with participants who may express suicidal ideation. She is registered in the student and doctoral candidates' registry of the Ordre des Psychologues du Québec, which permits her to directly assess and provide intervention to patients. [name]'s clinical PhD supervisor is available should she need to discuss participant follow-up or referral in the context of this current study.

The coach supervisor will attend monthly investigator meetings. She will use a fidelity checklist (adapted from one used in our previous research, see Appendix F - fidelity checklist) and will also blindly enter coaching data into blank copy of the coach log to monitor all coach contacts initially, until a satisfactory level of adherence to the directives in the coaching manual is attained. After this, s/he will monitor a sample (selected by the statistician) of calls using the checklist. Any discrepancies between the log of the coach and the log of the coach supervisor will be reviewed with the coach supervisor and the coach.

The coaches will record in their logs all contacts attempted and completed, duration of contacts, and tools that were recommended and/or used. Additionally, the coach will record whether the participant is setting goals independently or with prompting from the coach.

### **3.6 Randomization**

Participants will be randomized to Group 1 (tools only) or Group 2 (tools with coaching) by a computer-generated randomization schedule that uses random block sizes, with an allocation ratio of 1:1; SAS University Edition will be used. In order to ensure allocation concealment, the study coordinator will first verify eligibility and informed consent. Subsequently, the unique patient identifier (PID) from the recruitment log will be entered into the randomization schedule, along with: date of consent, date of baseline interview. An automated interface will then assign the participant to the study group. Participants will be stratified based on whether their symptoms are none to mild or moderate to severe to ensure an equal balance of symptom severity in both study groups. Participants will be categorized as none to mild if their PHQ-9 is less than 10 and their GAD-7 score is less than 10. Participants with a PHQ-9 score of 10 or more and/or a GAD-7 score of 10 or more will be categorized as being in the moderate to severe group.

### **3.7 Follow-up of at risk participants**

All research staff members who have patient contact are trained to follow-up on any reported suicidal thoughts to identify if there is intent to act. All patients who report only thoughts, but no intent, will be given the telephone numbers of local crisis/suicide hotlines. The coach supervisor will follow-up immediately with any participant who divulges suicidal intent. If the patient is deemed at risk, the patient's most responsible physician (as identified by the participant at that time) will be informed with the patient's consent. Furthermore, if the coach supervisor identifies any immediate risk of self-harm, the patient will be directed to the nearest emergency room, will

be given the telephone numbers of a suicide hotline and the most responsible physician will be informed (the police will be alerted if the patient with suicidal behaviours refuses to go to the emergency room). Those with suicidal intent identified at screening will be excluded from the study; those with suicidal intent during follow-up will be withdrawn from the study.

Participants with a PHQ-9 score of 20 or more will be encouraged to see their physician. If patients consent, the identified physician will be informed.

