#### **3.2 Sample and exclusion criteria**

We have already assembled a cohort of 267 patients 65+ years old for a previous study (PCAP study, see SMRC protocol #18-04). Among these, 80% (n=213) agreed to be contacted again for future research opportunities. These patients were discharged home following hospitalization between October 2018 and December 2019 at the medical or geriatric units of two general hospitals on the west island of Montreal. Among the original cohort, 40% were born outside Canada; 30% received homecare services, and 65% were high-risk for functional decline, death, and increased health care service utilization.

With anticipated 75% participation, we project a sample size of 160. Exclusion criteria for the current study will comprise: moderate to severe cognitive impairment (using BOMC a brief cognitive screen); unable to read in English or French (self-reported); hearing impairment (as judged by research staff); currently receiving counseling or psychological therapy (as these treatments may conflict with the self-care interventions); currently living in a long term care or other medicalized facility, or presenting suicidal intent (as identified through the final item of the PHQ-9 which will be asked at screening). Patients with suicidal intent will be contacted by the coach supervisor for further assessment and referral (see section 3.7 below). Patients receiving antidepressant or anxiolytic medications will be eligible for the study, as will all patients who do not meet the threshold for clinically-significant symptoms of depression and/or anxiety as they

may still benefit from the intervention Participants who begin counseling or psychological therapy after enrolment will not be withdrawn. Participants who are not eligible or interested in the study will be invited to contact 2-1-1 to follow-up on any needs (see [www.211qc.ca/en/](http://www.211qc.ca/en/)).

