### **3.9 Data analysis and statistical power**

Data analysis will be conducted and reported according to CONSORT guidelines. All the quantitative analyses will be carry out with SAS University Edition, STATA 15.0 and R Cran software.

The feasibility of the study will be described using the data collected as part of the study log, recruitment, refusal and uptake rates, completion of surveys, and the rates of missing data will be calculated.

Descriptive analyses will compare characteristics of participants associated with participation and completion of follow-up. Incomplete outcome data will constitute an important aspect of our study. Our general approach will be based on intention-to-treat (ITT) and Inverse Probability Weighting (IPW) will be used to handle missing data. Two sensitivity analyses will be carried out to validate the results obtained by IPW: 1) inclusion of subjects with complete data only; and 2) use of multiple imputation (MI) for missing data. Unless the primary outcome analyses yield different results for completers or MI vs IPW, the secondary analyses will be restricted to completers only.

Baseline imbalance will be assessed by comparing participants randomized to the 2 study arms with respect to 6 pre-specified baseline variables (AGE, SEX, hospital admitted to, COVID-19 DIAGNOSIS, PHQ-9, GAD-7); a maximum of 3 variables with clinically significant differences across arms will be identified.

The comparison of continuous outcomes between intervention and control groups will be based on a simple t-test; linear regression will be used to adjust for baseline imbalance (see above). Similarly, for binary outcome variables (CSQ), Pearson chi-square test and logistic regression will be performed. Effect sizes and 95% confidence intervals (95% CI) will be computed for all the analyses with a continuous outcome, and odds ratio and 95% CI for binary outcomes.

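### Participants with suicidal intent during follow-up are withdrawn from the whole study, so their 8-week scores are lost for a reason tied to the outcome

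*Protocol*

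**What the plan says.** Section 3.7 sets out the safety steps for suicidal thoughts and intent. It ends with a rule on status: intent at screening means exclusion, and "those with suicidal intent during follow-up will be withdrawn from the study". The protocol body does not say whether the 8-week interview is still held for these people.

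The same document treats another post-enrolment event the opposite way. Section 3.2 states: "Participants who begin counseling or psychological therapy after enrolment will not be withdrawn".

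The effectiveness outcomes are depression and anxiety severity at 8 weeks (section 2). Section 3.4 gives their collection: "At 8 weeks, with an anticipated follow-up rate of 75% (120 end of project interviews), the PHQ-9, and GAD-7 will be re-administered". The PHQ-9 and GAD-7 are otherwise described only at baseline.

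Section 3.9 adopts intention-to-treat, with inverse probability weighting (IPW) for missing outcomes, and complete-case analysis and multiple imputation (MI) as sensitivity analyses. Unless these give different results for the primary outcome, "the secondary analyses will be restricted to completers only".

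On contact before week 8, section 3.5 says "Coaches will contact participants a maximum of 3 times", in one arm only, and that coaches "will be trained to follow-up on any reported suicidal thoughts and to identify if there is intent to act".

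**The concern.** Stopping or changing a self-care intervention when someone discloses suicidal intent is sound clinical practice. Ending all participation is a separate step. It means that the 8-week score is not sought from people likely to be among the most distressed. Section 3.2 uses the final PHQ-9 item to identify suicidal intent at screening, and the PHQ-9 is also an outcome, so the reason for the missing score is bound up with the score.

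Two things follow. First, an SAP can choose how to analyse missing data, but it cannot recover scores that were never collected. Second, only the coached arm has scheduled contacts between baseline and week 8, so intent could come to light earlier, and more often, in that arm. Losing high scores mainly from the coached arm would make coaching look slightly better than it is.

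**Working it through.** **The plan's own figures.** Section 3.2 projects 213 × 0.75 = 159.75, about 160 participants, hence 80 per arm. Section 3.4 expects 160 × 0.75 = 120 interviews, hence 60 per arm. With 60 per arm, two-sided alpha 0.05 and an effect of 0.52 SD, power is 0.806 (noncentral t), which agrees with the stated 80%. Removing 1 to 3 completers from one arm lowers it only to 0.803 to 0.796. The issue is bias, not power.

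**Assumptions, none of them in the protocol.** In each arm m of 80 participants develop intent before week 8 (m = 0 to 3, or 0 to 3.75%). Non-cases complete at 0.75 and cases would have completed at rate c. Cases score g = 8 to 12 PHQ-9 points higher at week 8. The SD is 5, and the true difference between arms is zero.

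**Cases withdrawn in the coached arm only.** The coached mean then rests on non-cases alone, while the other arm keeps its cases:

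shift = −(m × c × g) / [(80 − m) × 0.75 + m × c]

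For m = 3, c = 0.75, g = 12: −(3 × 0.75 × 12) / (57.75 + 2.25) = −27/60 = −0.45.

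| m | c = 0.75, g = 8 | c = 0.75, g = 12 | c = 0.50, g = 8 | c = 0.50, g = 12 |
|---|---|---|---|---|
| 0 | 0 | 0 | 0 | 0 |
| 1 | −0.10 | −0.15 | −0.07 | −0.10 |
| 2 | −0.20 | −0.30 | −0.13 | −0.20 |
| 3 | −0.30 | −0.45 | −0.20 | −0.30 |

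**Partial imbalance.** Take m = 3 in each arm and c = 0.75, with 3 withdrawn in the coached arm and 1 in the other. The other arm keeps 2 cases, so the shift is −(2 × 0.75 × g) / (57.75 + 1.5): −0.20 for g = 8 and −0.30 for g = 12. Equal withdrawals give 0.

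**Scale, at c = 0.75.**
- Standard error of the difference: 5 × √(2/60) = 0.913. The shift is 0.10/0.913 = 0.11 to 0.45/0.913 = 0.49 of this.
- In SD units: 0.10/5 = 0.02 to 0.45/5 = 0.09.
- Against the detectable effect: 0.02/0.52 = 3.8% to 0.09/0.52 = 17.3%.

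**How much the planned methods would remove.** This was simulated with 4,000,000 normal baseline and week-8 score pairs. Intent was the top 1.25% or 3.75% of a latent score correlated 0.9 with the week-8 score, and a further 25% were lost at random. With baseline score as the only covariate, IPW or regression imputation left these shares of the complete-case shift:
- 92% at a baseline-to-week-8 correlation of 0.3
- 76–79% at 0.5
- 52–58% at 0.7

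Agreement between IPW, MI and complete cases would therefore not show that the loss was harmless. A shift this small is unlikely to make them disagree, so the completers-only rule for secondary analyses would probably stay in force.

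**The case against.** The strongest reply is that the clause sits in a safety section and does not say in so many words that data collection stops. The consent form or the coach manual, which were not available, might settle it. That is possible, but the rule in the protocol body is what staff would follow. It runs parallel to exclusion from the study at screening, and section 3.2 shows that withdrawal is a status the authors assign deliberately. Clear wording is needed even if only the intervention was meant.

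Several other points stand:
- The plan does not contradict intention-to-treat. Section 3.9 provides for missing outcomes in general, and no text says that collected scores are discarded. If intent first surfaces at the 8-week interview, no score need be lost.
- The imbalance between arms is a possibility that the text does not establish. Coaches act on reported thoughts, no routine suicide screen at calls is described, and section 3.7 covers all staff with patient contact.
- The score gap may be too large, since people found early receive immediate follow-up. At g = 2 to 4 and c = 0.75, the formula gives 0.75 × 2/60 = 0.025 to 3 × 0.75 × 4/60 = 0.15 points, or 0.005 to 0.03 SD, about 1% to 6% of 0.52 SD.
- The simulated percentages depend on the model. Baseline GAD-7, CAGE and service use could also enter the weighting or imputation.
- This is a pilot in which three of four objectives concern feasibility and acceptability. People with intent at screening are excluded and people with minimal symptoms are eligible, so there may be no cases at all.

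These points limit the size. They give no reason to stop seeking the outcome from these participants.

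**Conclusion.** The concern holds as a cheap improvement. As written, the rule ends study participation for an outcome-related reason, and methods working from the described baseline data would only partly make up the loss. Under the stated assumptions, 1 to 3 cases withdrawn in the coached arm alone shift the PHQ-9 comparison by 0.07 to 0.45 points (0.01 to 0.09 SD) in favour of coaching, which is always less than half a standard error. The shift is smaller if the gap in scores is smaller, and zero if there are no cases or withdrawals are equal by arm. It does not threaten the trial. Confidence is medium, because the rate, SD, score gap and imbalance are all assumed and the reading rests on the ordinary sense of the clause.

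**What to change.** Leave every safety step in section 3.7 unchanged and reword only the last clause. Participants with suicidal intent during follow-up should stop or adapt the intervention as clinically indicated and remain in the intention-to-treat set. Data already collected should be kept, including scores from an 8-week call at which intent surfaces. The 8-week interview should still be offered where the person agrees and it is clinically appropriate. Report these events by arm and by how they came to light (coach call, 8-week interview, other).

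The cost is one reworded clause, a check that the consent form matches, a clinical decision about re-contact in each case and, at the assumed 0 to 3 cases per arm, 0 to 6 extra calls in total. Some of the most severe cases may still be missing, because the interview depends on agreement and clinical judgement.
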